## Abstract

**Introduction:**

There is currently no gold standard or specific nutritional assessment tool to assess malnutrition in patients with nasopharyngeal carcinoma (NPC). Our study aims to develop a new nutritional assessment tool for NPC patients.

**Methods and analysis:**

NPC patients will be required to complete a risk factor questionnaire after obtaining their informed consent. The risk factor questionnaire will be used to collect potential risk factors for malnutrition. Univariate and multivariate logistic regression analyses will be used to identify risk factors for malnutrition. A new nutritional assessment tool will be developed based on risk factors. The new tool’s performance will be assessed by calibration and discrimination. The bootstrapping will be used for internal validation of the new tool. In addition, external validation will be performed by recruiting NPC patients from another hospital.

**Discussion:**

If the new tool is validated to be effective, it will potentially save medical staff time in assessing malnutrition and improve their work efficiency. Additionally, it may reduce the incidence of malnutrition and its adverse consequences.

**Strengths and limitations of this study:**

The study will comprehensively analyze demographic data, disease status, physical examination, and blood sampling to identify risk factors for malnutrition. Furthermore, the new tool will be systematically evaluated, and validated to determine their effectiveness. However, the restricted geographical range may limit the generalizability of the results to other ethnicities. Additionally, the study does not analyze subjective indicators such as psychology.

**Ethics and dissemination:**

The ethical approval was granted by the Ethical Committee of the First Affiliated Hospital of Guangxi Medical University (NO. 2022-KT-GUI WEI-005) and the Second Affiliated Hospital of Guangxi Medical University (NO. 2022-KY-0752).

**Clinical trial registration number:**

ChiCTR2300071550.

## 1 Introduction

Nasopharyngeal carcinoma (NPC) is a prevalent head and neck malignancy characterized by high invasiveness and early metastasis. Patients with NPC are often diagnosed at an advanced stage due to the lack of early symptoms [1]. While relatively rare in comparison to other types of cancer, there were 133,354 new cases of NPC in 2020 [2]. However, the distribution of NPC cases is highly geographically skewed, with over 70% of new cases occurring in East and Southeast Asia [3, 4]. A recent study has shown that in 2020, the provinces of Hainan, Guangxi, and Guangdong in southern China had the highest rates of years of life lost due to NPC among all provinces in China [5]. Furthermore, the proportion of NPC-related deaths among all cancer deaths in China remained at approximately 1.0% from 2005 to 2020. However, the overall number of NPC-related deaths increased by 7.3% over the same period [5].

The prevalence of malnutrition in cancer patients worldwide is reported to range from 20% to over 70% [6]. The deleterious effects of malnutrition in cancer patients have been well documented, including weight and muscle loss, compromised immune function, increased susceptibility to infections, psychosocial stress, diminished quality of life, and treatment toxicity [6]. According to recent research, the occurrence of malnutrition among NPC patients varies from 5.3% to 94.8% [7–9]. Malnutrition in NPC patients may compromise the immune system, prolong hospitalization, and diminish the effectiveness of treatment [10–12]. Moreover, several studies have suggested that there is a correlation between malnutrition and poor survival outcomes in NPC patients [13].

Prevention of malnutrition is feasible through early identification of at-risk patients. To comprehensively manage malnutrition in hospitals, all patients should be systematically screened for nutritional risk on admission, and a detailed assessment of the nutritional status of those identified as being at high risk should be carried out [14]. Subsequently, malnourished or high-risk patients should receive individualized nutritional interventions that are suitable for their specific needs [15]. Although the importance of this process is recognized, it is not consistently implemented. A “NutriDay” survey comprising 21,000 patients across 325 hospitals in 25 European countries showed that established detection routines for malnutrition were only implemented in 52% of hospitals (with a range of 21% to 73%) [16]. Although malnutrition is common and nutritional assessment is critical, there is currently no universally accepted standard for nutritional assessment [17, 18]. However, commonly used malnutrition assessment tools have limitations [19]. For example, PG-SGA is complex and time-consuming, and its results also depend on the experience of the observer [37]. While GLIM remains an expert consensus, and its clinical effect still needs to be verified [38]. The applicability of MNA to Asians may be limited due to the absence of race-specific metrics, and the definition of BMI in MNA may need to be adapted to account for racial differences [19]. To address these gaps, the study aims to develop a specific tool for assessing malnutrition in NPC patients. The new tool has significant advantages. It not only has easily obtainable assessment indicators, saving time, but also includes evaluation indicators specific to the nutritional risk factors of NPC patients. The tool may provide a more personalized and accurate assessment for NPC patients.

## 2 Methods and analysis

The primary aim is to develop and validate a new nutritional assessment tool for NPC patients that is based on risk factors for malnutrition. The research timeline spans from June 2023 to April 2024 and will be conducted through a two-phase approach. We have access to information that could identify individual participants during or after data collection.

### 2.1 The Phase I

#### 2.1.1 Objectives

The aim of Phase I is to develop, evaluate, and internally validate a new nutritional assessment tool for NPC patients.

#### 2.1.2 Study design

The study is designed as a prospective, cross-sectional diagnostic study.

#### 2.1.3 Study settings and participants

The study will be conducted at the First Affiliated Hospital of Guangxi Medical University, Nanning, Guangxi, China, from June 2023 to December 2023.

Eligible participants for the study will be recruited in June 2023 based on predefined inclusion and exclusion criteria.

(1) Inclusion criteria(i) Patients with newly diagnosed NPC confirmed by pathology; (ii) Patients aged more than 18 years; (iii) Patients who have no history of other malignancies than cancer.(2) Exclusion criteriaPatients who have life-threatening diseases, mental disorders, or intellectual disabilities will be excluded.

#### 2.1.4 Study tools

(1) The risk factor questionnaireThe risk factor questionnaire includes the following potential risk factors: socio-demographic data (gender, BMI, and age), lifestyle habits (smoking and drinking history), treatments (the number of chemotherapy cycles and radiation treatments), disease state (acute or chronic inflammation, tumor stage), anthropometry (measured by calf circumference), and blood indices (hemoglobin, total protein, albumin, pre-albumin, and retinol-binding protein).(2) The Patient-Generated Subjective Global Assessment (PG-SGA)The PG-SGA is a comprehensive tool designed to assess malnutrition in cancer patients [20]. The PG-SGA evaluates seven aspects, which include body weight, food intake, symptoms, activity and physical function, disease and nutritional needs, metabolic needs, and physical examination [20]. The patient evaluates the first four aspects, while medical staff assess the last three. The PG-SGA score ranges from 0 to 1 for no malnutrition, 2 to 3 for suspicious or mild malnutrition, 4 to 8 for moderate malnutrition, and ≥9 for severe malnutrition [20].

#### 2.1.5 Sample size

The sample size calculation was based on previous research conducted by Riley et al. [21]. We included 15 predictor variables in the risk factor questionnaire. Based on the findings reported by Song et al. [22], a PG-SGA score of 2 or higher was utilized as a diagnostic criterion for malnutrition. The incidences of malnutrition and well-nourished in NPC patients were 0.599 and 0.401, respectively [22]. For logistic regression models with outcome proportions of 0.4, the corresponding max(R^2^_cs_) value is 0.74 [21]. For binary outcome, R^2^_cs_ = 0.5* max(R^2^_cs_) = 0.37. The sample size was calculated using the R language (version 4.2.1) with the pmsampsize package. The programming to calculate sample size was “(type = “b”, rsquared = 0.37, parameters = 15, prevalence = 0.401)”. After comparing the calculated sample sizes, the largest sample size was 370.

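### The 370 is set by precision of the overall proportion; it also limits overfitting to a shrinkage of 0.9 only if R²cs reaches about 0.30 (AUC about 0.83), and the assumed 0.37 is not explained

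*Protocol article*

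**What the plan says.** Section 2.1.5 starts from the number of candidates: "We included 15 predictor variables in the risk factor questionnaire". It takes the outcome split from a cited survey: "The incidences of malnutrition and well-nourished in NPC patients were 0.599 and 0.401, respectively". From a cited methods paper it takes the ceiling on R²cs: "For logistic regression models with outcome proportions of 0.4, the corresponding max(R^2^_cs_) value is 0.74". The anticipated value follows in one sentence: "For binary outcome, R^2^_cs_ = 0.5* max(R^2^_cs_) = 0.37". These go into pmsampsize as "rsquared = 0.37, parameters = 15, prevalence = 0.401", and the section concludes: "After comparing the calculated sample sizes, the largest sample size was 370". It does not say which criterion gave the largest size, and it does not state the target shrinkage, the permitted optimism or the precision margin.

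Section 2.1.4 lists the candidates without their coding, for example "disease state (acute or chronic inflammation, tumor stage".

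Sections 2.1.7 and 2.1.8 screen the candidates at a univariable p-value below 0.1, fit a multiple logistic regression, and turn the result into equations and a nomogram. The 200 bootstrap replications are described only as yielding ROC curves and AUC values.

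**The concern.** R²cs is not fixed by the outcome being binary. On the section's own ceiling it can lie anywhere from 0 to 0.74. Taking half of the ceiling is a judgement, made before any data, about how well the model will predict. The wording presents it as a rule, and the article gives no earlier model, R² or AUC to support it.

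The reader therefore cannot see how far the protection against overfitting depends on that judgement. If the model predicts less well, the coefficients from 370 patients will be too extreme. The nomogram would then give risks too high for high-risk patients and too low for low-risk ones. Nothing described in 2.1.7 or 2.1.8 would correct this before the tool is issued.

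**Working it through.** **Inputs from 2.1.5.** p = 15 parameters, proportion φ = 0.401, R²cs = 0.37.

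**Inputs assumed** (program defaults, not stated in the article). Target shrinkage S = 0.90, optimism in R² of 0.05, margin of ±0.05 for the overall proportion.

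**Step 1: the ceiling.** max R²cs = 1 − (0.401^0.401 × 0.599^0.599)² = 0.740, which agrees with the article's 0.74. Half of this is 0.37, a Nagelkerke R² of 0.50.

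**Step 2: reproduce 370.**
- Shrinkage: n = p / [(S − 1) ln(1 − R²cs/S)] = 15 / [(−0.1) ln(1 − 0.37/0.9)] = 283.3, so 284.
- Optimism: the same formula with S = 0.37 / (0.37 + 0.05 × 0.740) = 0.909 gives 315.8, so 316.
- Overall proportion: n = (1.96/0.05)² × 0.401 × 0.599 = 369.1, so 370.

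The largest is 370, an exact match. The third formula contains neither R²cs nor p.

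**Step 3: where the shrinkage criterion would overtake 370.** Solving it for R²cs at n = 370 and p = 15: R²cs = 0.9 × [1 − exp(−15/(0.1 × 370))] = 0.9 × (1 − 0.667) = 0.300, a Nagelkerke R² of 0.405.

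**Step 4: translate to AUC.** R²cs was converted by numerical integration at φ = 0.401, once with an equal-variance binormal linear predictor and once with a normal one. The two agree closely. R²cs 0.37 corresponds to AUC 0.87, and R²cs 0.30 to AUC 0.83.

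**Step 5: consequence at 370 patients and 15 parameters.**

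| True AUC | R²cs | n needed for S = 0.9 | Expected shrinkage at 370 |
|---|---|---|---|
| 0.83 | 0.302 | 367 | 0.90 |
| 0.80 | 0.253 | 455 | 0.88 |
| 0.75 | 0.179 | 677 | 0.83 |
| 0.70 | 0.117 | 1081 | 0.76 |

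**Step 6: parameter count.** The list in 2.1.4 has 15 variables: gender, BMI, age, smoking, drinking, chemotherapy cycles, radiation treatments, inflammation, tumor stage, calf circumference and five blood indices. Fifteen parameters is therefore right if each takes one term. At R²cs 0.37 the overall requirement stays at 370 for 17 parameters (the overfitting criteria give 322 and 358). It becomes 379 for 18 and 422 for 20, both set by the optimism criterion. For a shrinkage of 0.9 at 370 patients, the AUC needed rises to about 0.85 with 17 parameters and 0.87 with 20.

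**The case against.** Three stronger readings are tempting, and the document supports none of them.

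- **That 370 is a miscalculation, or is produced by the choice of 0.37.** It reproduces exactly, and with 15 parameters it is unchanged for any R²cs of 0.30 or more. What depends on 0.37 is whether 370 is also enough against overfitting.
- **That 15 is the wrong parameter count.** The coding is not given. Section 2.1.7 names graded variables as a class of their own, which is compatible with a single ordered term for stage. Coding is also a detail that an article may leave to a fuller document. The count matters only if it reaches 18.
- **That the tool will be clearly overfitted.** This is a cross-sectional diagnostic model, and BMI and calf circumference are close to the body weight and physical examination that PG-SGA itself scores. A high AUC is plausible. Just below the threshold the loss is gradual: 0.88 against a target of 0.90 at AUC 0.80.

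Two further points are fair. The methods paper cited for the ceiling may discuss the factor of one half; that cannot be checked here, so the criticism is only that the article does not explain the choice. And 2.1.5 never claims that 370 is sufficient: the discussion calls the sample large, while the limitations section calls it limited.

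The calibration plots and the external validation at the second hospital could reveal overfitting. They do not remove it from the coefficients. What remains is an influential assumption worded as a rule, and a tool built without shrinkage.

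**Conclusion.** The point holds as a matter of justification and disclosure, not of arithmetic. The 370 is correct for the overall proportion under the assumed default margin. As protection against overfitting it is conditional: with 15 one-term predictors and an assumed shrinkage target of 0.9, it needs R²cs of at least about 0.30 (AUC about 0.83). The article assumes 0.37 (AUC about 0.87) without saying why. If the true AUC is 0.75 or 0.70, expected shrinkage falls to 0.83 or 0.76. The documents give no basis for saying which AUC will be reached. The concern about the parameter count is conditional on coding that is not stated.

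**What to change.** Keep 370 patients.

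In 2.1.5, replace the sentence that derives 0.37 from the outcome type with a statement that it is an assumption, equivalent to an AUC of about 0.87. Say that 370 was set by the precision of the overall proportion, state the defaults used, and add that a shrinkage of 0.9 at this size needs R²cs of about 0.30. Count model parameters after coding rather than questionnaire variables, and confirm that the total is no more than 17 if 370 is to remain the largest requirement at R²cs 0.37.

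In 2.1.7 and 2.1.8, use the 200 bootstrap replications already planned, repeating the univariable screening and the model selection in each, to estimate the calibration slope. Apply that slope to the coefficients as a shrinkage factor before the nomogram is drawn. Fitting a penalised model instead would also serve.

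The cost is slightly more analysis work and a less favourable stated property of the sample size. No extra patients or data collection are needed.

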#### 2.1.6 Data collection

We will use the risk factor questionnaire and PG-SGA to collect data. Data will be collected through face-to-face interviews, clinical examinations, and anthropometric measurements. To ensure data quality, the investigator responsible for data collection will have their work checked by another investigator, with any discrepancies to be resolved through a discussion between the investigators. The data collection process will continue until the targeted sample size has been attained.

#### 2.1.7 Data analysis

The analysis of the data will be performed using SPSS 26.0 and R software 4.2.1. Quantitative data will be presented using medians with interquartile ranges [P25, P75] and means ± standard deviations. For univariable analysis, we employed the t-test, chi-squared, and Wilcoxon rank-sum tests for continuous, categorical, and graded or skewed distribution variables, respectively. Variables with p-values less than 0.1 will be selected for the multiple logistic regression model, with variables having a p-value less than 0.05 considered statistically significant. The nomogram and calibration plot will be generated using the “rms” package of R software 4.2.1. The receiver operating characteristic (ROC) curves will be plotted, and the area under the ROC curve (AUC) values will be calculated using the “pROC” package of R software 4.2.1. Double-checking of data entry will be implemented to ensure consistency.

#### 2.1.8 Study procedure

Three hundred and seventy NPC patients will be recruited at the First Affiliated Hospital of Guangxi Medical University.NPC patients will be divided into well-nourished and malnourished groups according to the PG-SGA. The risk factor questionnaire will be used to collect potential risk factors for malnutrition in NPC patients. These potential risk factors will be analyzed using univariate and multivariate logistic regression analyses to identify risk factors for malnutrition in NPC patients.Based on the identified risk factors, a set of mathematical equations for a new nutritional assessment tool will be developed. The tool will be graphically represented as a nomogram. Our aim is to provide a visual and intuitive method that enables healthcare professionals to quickly assess an individual’s risk of malnutrition based on specific risk factors.The new tool’s performance will be evaluated using measures of discrimination and calibration. Specifically, discrimination will be assessed by the ROC curve and AUC value, while calibration will be evaluated using a calibration plot.The internal validation of the new tool will involve bootstrapping with 200 replications. ROC curves will be generated, and AUC values will be calculated.

### 2.2 The Phase II

#### 2.2.1 Objectives

The aim of Phase II is to externally validate the new nutritional assessment tool.

#### 2.2.2 Study design

The study is designed as a prospective, cross-sectional diagnostic study.

#### 2.2.3 Study settings and participants

The study will be conducted at the Second Affiliated Hospital of Guangxi Medical University, Nanning, Guangxi, China, from January 2024 to April 2024.

Eligible participants for the study will be recruited in January 2024 based on predefined inclusion and exclusion criteria. The inclusion and exclusion criteria for participant eligibility in this phase are the same as in Phase I.

#### 2.2.4 Study tools

The new tool and PG-SGA will be the study tools in Phase II.

#### 2.2.5 Sample size

Currently, there are no generally accepted methods for calculating the sample size required for external validation of risk prediction models. However, prior investigations [23, 24] have put forth a recommendation that external validation studies should incorporate no fewer than 100 events and 100 nonevents to ensure accurate and precise estimates of performance measures. Thus, to comply with this recommendation, at least 100 well-nourished NPC patients and 100 malnourished NPC patients will be recruited to validate the new tool in Phase II.

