#### 2.2.6 Data collection and analysis

The new tool and PG-SGA will be used to collect data to assess malnutrition in NPC patients. The external validation will be performed using the ROC curve, AUC value, and calibration plot. The ROC curve will be performed, and the AUC value will be calculated using MedCalc software. The calibration plot will be generated using the “rms” package of R software 4.2.1.

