#### 2.2.7 Study procedure

At the Second Affiliated Hospital of Guangxi Medical University, 100 well-nourished and 100 malnourished NPC patients will be recruited, using PG-SGA as the standard for malnutrition assessment.The new tool will be utilized to assess the nutritional status of these 200 NPC patients.The assessment results obtained with the new tool will be analyzed against the PG-SGA to calculate AUC for evaluating NPC patients’ nutritional status. Additionally, ROC curves and calibration plots will be generated to visually demonstrate the accuracy and reliability of the new tool.

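### Phase II shows calibration only by a plot, in a sample fixed at 100:100 that displaces that plot by about 0.40 on the logit scale, and names no calibration slope with an interval

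*Protocol article*

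**What the plan says.** Section 2.2.5 gives no precision target of its own. It takes over a recommendation from earlier work of "no fewer than 100 events and 100 nonevents to ensure accurate and precise estimates of performance measures" and concludes that "at least 100 well-nourished NPC patients and 100 malnourished NPC patients will be recruited to validate the new tool in Phase II".

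Section 2.2.6 lists the measures: "The external validation will be performed using the ROC curve, AUC value, and calibration plot". Section 2.2.7 fixes the recruitment: "100 well-nourished and 100 malnourished NPC patients will be recruited, using PG-SGA as the standard for malnutrition assessment". It then says "The new tool will be utilized to assess the nutritional status of these 200 NPC patients", and states what the displays are for: "ROC curves and calibration plots will be generated to visually demonstrate the accuracy and reliability of the new tool".

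For Phase I, section 2.1.5 states the outcome mix expected in this population: "The incidences of malnutrition and well-nourished in NPC patients were 0.599 and 0.401, respectively". The same section assumes a Cox-Snell R² of 0.37 with 15 parameters. No expected AUC is given anywhere.

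**The concern.** The tool is a nomogram that gives each patient a risk of malnutrition, so its probabilities have to be right as well as its ranking. The bootstrap outputs named in section 2.1.8 are ROC curves and AUC values, which concern ranking. Phase II is therefore the only named check of calibration in new patients.

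Two features of the plan weaken that check. First, the outcome mix is set by design at 1:1, which moves the calibration plot away from the diagonal even if the tool is sound. Second, the plot comes with no named estimate or interval, although 200 patients pin calibration down less well than they pin down the AUC. A displaced, noisy curve could be described as showing reliability, or a sound tool could be read as miscalibrated, and nothing named in the plan would settle which.

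**Working it through.** **The plan's own figures.** Phase II is 100 + 100 = 200, which follows the cited rule; there is no formula to reproduce. For Phase I, with R² 0.37, 15 parameters, prevalence 0.401 and the default settings (shrinkage 0.9, margin 0.05), the three criteria give 284, 316 and 370 patients. The maximum is 370 and the maximum R² is 0.740, as section 2.1.5 states.

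**Displacement of the plot.** Sampling on the outcome shifts the logit intercept by ln(sampled odds) − ln(natural odds) = ln(1) − ln(0.599/0.401) = −0.40. If Phase I has the expected mix and the tool is perfectly calibrated there, the expected observed proportion at predicted risk q is expit(logit q − 0.40):

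| Predicted | Expected observed at 1:1 |
|---|---|
| 0.20 | 0.14 |
| 0.40 | 0.31 |
| 0.60 | 0.50 |
| 0.80 | 0.73 |

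**Precision at 100/100.** The AUC is not in the protocol, so 0.70 to 0.90 is an assumption. The linear predictor is taken as normal in each outcome group, with SD s = √2·Φ⁻¹(AUC) and mean difference s², so that the true slope is 1. The slope's SE comes from the Fisher information of logit P(Y=1) = a + b·LP. The AUC's SE is by Hanley–McNeil. Half-widths are 1.96 × SE.

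| AUC | Slope SE | Slope half-width | AUC half-width |
|---|---|---|---|
| 0.70 | 0.216 | 0.42 | 0.07 |
| 0.75 | 0.180 | 0.35 | 0.07 |
| 0.80 | 0.158 | 0.31 | 0.06 |
| 0.85 | 0.144 | 0.28 | 0.05 |
| 0.90 | 0.137 | 0.27 | 0.04 |

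Simulation agrees, with a slope half-width of 0.43 at AUC 0.70. Under this model the protocol's R² of 0.37 corresponds to an AUC of about 0.86 to 0.87, a slope SE of 0.141 and a half-width of 1.96 × 0.141 = 0.28.

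**What that precision can show.** For a tool with true slope b below 1, SE(b) = b × SE(1). The chance that the 95% CI excludes 1 is roughly Φ((1 − b)/(b·SE(1)) − 1.96). At R² 0.37 and b = 0.8, this is Φ(0.2/(0.8 × 0.141) − 1.96) = Φ(−0.19), or about 0.43; the typical interval is 0.58 to 1.02. In simulation (3,000 validations per AUC):

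| AUC | True slope 0.8 | True slope 0.7 |
|---|---|---|
| 0.70 | 22% | 48% |
| 0.75 | 28% | 60% |
| 0.80 | 36% | 71% |
| 0.85 | 39% | 76% |
| 0.90 | 42% | 77% |

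For 0.8, the formula gives 44% at AUC 0.90, hence the range of 22–44%. For 0.7, the formula is more optimistic (51–88%) because it ignores the skewness of the slope estimate, so the simulated figures are used. For a true slope of 0.6, detection is about 80–96%.

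**The case against.** **An unseen analysis plan may add a slope and interval.** This is fair, and the absence of such detail from an article would not be a finding by itself. What the article does state is the list of measures, the fixed 1:1 recruitment, and the purpose of demonstrating reliability visually. An added slope would not remove the displacement of the plot. Nor do the documents say that visual inspection is the sole criterion.

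**The precision wording is a cited recommendation, and the size is a floor.** This also stands. A reader might infer that the protocol makes a false precision claim of its own. The documents do not support that: the phrase is attributed to earlier work, is reasonable for the AUC, and section 2.2.5 says at least 100 per group. Section 2.2.7, however, fixes 100 and 100.

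**Clear overfitting would usually be caught.** A reader might infer that 200 patients would usually fail to expose a clearly overfitted tool. The figures do not bear that out. Once a slope is computed, 0.7 is detected in about half to three quarters of studies and 0.6 in most. Only milder overfitting, near 0.8, would usually be missed. On the plan's own inputs the expected shrinkage is 1 + 15/(370 × ln 0.63) = 0.91, so slopes of 0.7 to 0.8 lie outside its assumptions. An optimistic R² or the p-value selection of predictors in section 2.1.7 could lead there.

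**The slope is not the only usable measure.** Correct. It is unaffected by outcome-based sampling only if the logit is linear in the tool's predictor, and a plot corrected for the outcome mix would also serve.

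**The remedy adds no precision.** True. It makes the available precision visible.

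**Conclusion.** The point holds as a flaw in how calibration is to be assessed and described. It does not show that Phase II is too small for its AUC. With recruitment at 1:1, the plot of a sound tool is displaced by about 0.40 on the logit scale, and the named methods give no way to tell this from noise or overfitting.

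The slope's half-width is about 0.28 in the protocol's own scenario. The wider figure of 0.43 requires an assumed AUC near 0.70, so ±0.4 should not be read as the plan's expected precision.

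The displacement assumes that Phase I shows the expected 0.599/0.401 mix and that Phase II is held to 100 and 100. If Phase II instead recruited at natural prevalence until both minimums were met, as section 2.2.5 alone would allow, this design-induced displacement would not arise. The precision figures rest on a normal linear predictor within each outcome group.

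**What to change.** - **Sections 2.2.6 and 2.2.7:** state that the Phase I equation is applied unchanged, and that the calibration slope is estimated by logistic regression of PG-SGA class on the tool's linear predictor and reported with its 95% CI. Note the linear-logit condition.
- **Plot and intercept:** keep the plot as illustration. Report it and the intercept only after correction for the sampled outcome mix, or if recruitment is at natural prevalence.
- **Section 2.2.5:** say that 100/100 is adequate for the AUC (about ±0.04 to 0.07), and give the slope precision (about ±0.28 at R² 0.37; ±0.27 to 0.43 for an assumed AUC of 0.90 to 0.70).
- **Section 2.2.7:** tie the accuracy and reliability wording to these intervals.

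The cost is a few lines of text, one regression and a less favourable precision statement. No extra patients are needed.
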